# Implementation of an in situ simulation-based training adapted from Morbidity and Mortality conference cases: effect on the occurrence of adverse events—study protocol of a cluster randomised controlled trial

**DOI:** 10.1186/s13063-022-06040-2

**Published:** 2022-02-02

**Keywords:** Patient safety, In situ simulation training programme, Inter-professional teamwork, Cluster randomised controlled trial, Trigger tool, Adverse event, Evaluation, Change management

## Abstract

**Background:**

Morbidity and Mortality conference provides the necessary improvement measures for patient safety. However, they are an underused resource mainly because the conclusions to be drawn from the discussion and their implications for practice are not always well integrated by inpatient care teams. We therefore propose in this study two interventions to optimise their effectiveness: a passive feedback with wide dissemination by e-mail and/or on paper of the results of the Morbidity and Mortality conference to inpatient care teams and an active feedback with in situ inter-professional simulation-training programme in which scenarios will be based on cases studied in Morbidity and Mortality conference. In the present study, we hypothesise that the greatest reduction the occurrence of adverse event will be in the active feedback arm.

**Methods:**

A cluster randomised controlled study will be performed at four study sites. The unit of randomisation is wards within the study sites. Fifteen wards will be randomly assigned to passive feedback, active feedback, or a standard MMC (control arm). Passive feedback and active feedback arms will be compared to standard arm in terms of occurrence of adverse events. The trigger tool methodology used to identify adverse events is a retrospective review of inpatient records using “triggers”: an adverse event is defined as a patient’s stay with at least one positive trigger.

**Discussion:**

The in situ simulation training based on cases processed in Morbidity and Mortality conference is built according to the main topics identified for the successful implementation of healthcare simulation in patient safety programmes: technical skills, nontechnical skills, assessment, effectiveness, and system probing. The in situ simulation-training programme conducted as part of the study has the potential to improve patient safety during hospitalisation. We therefore expect the greatest reduction in the occurrence of adverse events in patients hospitalised in the active feedback arm. This expected result would have a direct impact on patient safety and would place in situ simulation at the highest level of the Kirkpatrick model.

**Trial registration:**

Clinicaltrials.gov NCT02771613. Registered on May 12, 2016. All items from the WHO Trial Registration Data Set can be found within the protocol.

**Supplementary Information:**

The online version contains supplementary material available at 10.1186/s13063-022-06040-2.

## Background

Any human activity that presents a potential risk develops the analysis of adverse outcomes to learn from mistakes made [1]. In the medical field, Morbidity and Mortality conferences (MMC) have been used for more than 100 years, first in the USA and then around the world, to improve practice by examining medical errors and poor outcomes [2–5]. MMC is defined as a collective, retrospective, and systemic analysis of cases involving death, complication, or event that could have caused harm to the patient, with the objective of implementing actions to improve patient care [3]. MMCs provide the necessary improvement measures for patient safety and professional learning [6–10]. Nowadays, MMCs exist in many healthcare organisations but is a resource that is not used to its full potential mainly because the conclusions to be drawn from the analyses/discussions and their implications for change in practice and behaviour are not always well implemented by inpatient care teams [11, 12]. In our university hospital federation (*Hospices Civils de Lyon*, Lyon, France), despite the existence of an online procedure to prepare and standardise MMCs, two major obstacles have been identified for optimal efficiency: on the one hand, the lack of dissemination of information from return of experience, and on the other hand, the lack of effective implementation of corrective measures, most often due to the absence of a person responsible for the application and follow-up of this feedback [13]. As a result, there is a need for effective and achievable methods to improve the implementation, monitoring, and effectiveness of MMCs. The MMC Simulation project described herein (in situ simulation-based training adapted from MMC cases) tries to fill these gaps by designing a training programme using innovative methods. This is based on simulation-based teaching, an increasingly applied, evidence-based, teaching method [14]; in situ simulation-based training is defined as a simulated session in the exact environment in which it is intended to take place, as opposed to simulation centres, and which is particularly adapted for team training within an institution [15]. The latter can be an interesting method to improve care delivery in high pressure situations requiring the coordination of many people, actions, and resources; it is inter-professional and aims to raise the team’s awareness of the factors that have contributed to local events [16]. The goal is the appropriation of corrective measures*.* However, few studies have evaluated whether such interventions can improve the quality of inpatient care [17, 18] and, prior to the trial described herein, no study has evaluated the impact of these interventions on adverse events related to the care provided.

We hypothesise that the greatest reduction the occurrence of adverse event will be in the active feedback arm (in situ simulation-training programme with scenarios adapted to the clinical cases processed in MMC) than in the passive feedback arm (wide dissemination by e-mail and/or paper of the results of the MMC) and standard control arm. In the present report, we describe the methodology, and analytical plan for the MMC Simulation project.

### Study design

A cluster randomised controlled study constituted by three arms will be conducted. The cluster units will be wards in the participating hospitals. After agreement to participate by the medical head of the wards, the wards will be randomly assigned to passive feedback, active feedback, or standard MMC (control arm) based on computer-generated randomisation sequence with a 1:1:1 treatment allocation ratio, stratified by centre. For methodological reasons, wards of the same specialty will belong to different hospitals in order to reduce the risk of contamination. The planned duration of the intervention is 2 years. Data will be collected at three points of assessment: (1) during 1 year prior to the intervention (pre-measurement), (2) for 2 years, starting 6 months after the start of the procedure, and (3) during 1 year after the end of the intervention (follow-up measurement) in case of significant results. Adverse event rates will be compared between arms before and during the intervention following a difference-in-difference analysis. Figure 1 illustrates the study process.

**Fig. 1 Fig1:**
[figure not shown]
Study process

### Study setting and recruitment

The Lyon University Hospital Federation (*Hospices Civils de Lyon* [HCL]) is a federation of academic healthcare organisations. The study concerns 15 wards among 4 hospitals (3 multidisciplinary and 1 specialised) located in Lyon (France). Figure 2 provides an overview over the submodules.

**Fig. 2 Fig2:**
[figure not shown]
Distribution of hospital wards in the study arms

The ward specialties were chosen in accordance with the legislation of the French National Authority for Health (HAS), which has made mandatory MMC in “at risk” specialties (obstetrics, surgery, emergency, and intensive care) in the context of hospital accreditation [25]. Accordingly, surgical and trauma intensive care unit, orthopaedic surgical unit, general and digestive surgical unit, emergency room, and obstetric unit are included in the study. In those 15 wards, we will monitor outcomes among all stays in conventional hospitalisation at the exception of patients in hospitalisation by day and patients under 18 years of age.

### Sample size

#### Number of subjects expected

Over the entire study period, all stays of patients who stayed in the participating wards will be operated by the data management and analysis department (HCL) in order to measure the evaluation criteria of the trial. In total, we expect to include approximately 40,000 stays in the 1-year period before the intervention phase and 80,000 stays during the 2 years of the intervention phase.

#### Minimal effect demonstrable

Following the methodology introduced by Preisser et al. [26], we estimated the minimal demonstrable effect at a 44% reduction of adverse events in the intervention arms versus the control arm.

This estimation was based on the following assumptions: a baseline major adverse events rate of 10% for both control and intervention arms [27, 28], a post-intervention AE rate stable at 10% in the control arm, alpha risk at 5%, power at 80%, within-time ICC and between-time ICC at 0.026 and 0.022 respectively, a mean 2500 stays per ward and per year, and finally at least 40,000 stays per period (13,333 stays per arm and per period, accounting for about 5 wards).

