We will then conduct multivariate analyses to model the effect of the intervention on the adverse event rate by adjusting for the arm (control, passive and active feedback), the period (before and during intervention), and arm-period interaction. We will also consider the different identified predictors or potential confounding factors. A mixed effects logistic regression model will be developed using the NLMIXED procedure to take into account the two-level hierarchical structure of the data (“stay” level nested within a “ward” level). This type of model will make it possible to measure the degree of similarity between patients of the same cluster and the variability of the endpoint between clusters. A generalised estimation equation (GEE) model approach will also be tested if relevant using the GENMOD procedure. Quantitative variables will be considered in their continuous form, except if the assumption of linearity with the endpoint studied was not verified. Possible interactions will also be sought and taken into account in the model.

All confidence intervals will be calculated at 95%, and statistical test results will be presented at the 5% threshold. Tests will be bilateral and based on non-parametric statistics if necessary. All analyses will be performed using SAS software (SAS Institute Inc., Cary, NC, USA).

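### The 44% detectable reduction at 80% power makes no apparent allowance for having only 15 wards; with a t reference, power at 44% is about 69–74% and the detectable reduction about 47–50%

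*Protocol article*

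**What the plan says.** Under Sample size, Minimal effect demonstrable, the protocol article states: "we estimated the minimal demonstrable effect at a 44% reduction of adverse events in the intervention arms versus the control arm". The listed assumptions are:

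- "a baseline major adverse events rate of 10% for both control and intervention arms"
- "a post-intervention AE rate stable at 10% in the control arm"
- "alpha risk at 5%, power at 80" (per cent)
- "within-time ICC and between-time ICC at 0.026 and 0.022 respectively"
- "a mean 2500 stays per ward and per year"
- "13,333 stays per arm and per period, accounting for about 5 wards"

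The method is attributed to a cited publication. Study design fixes wards as the randomised units, 1:1:1 allocation and a difference-in-difference comparison. Study setting and recruitment fixes 15 wards. Data analysis specifies a logistic mixed model with a ward level, and says "Tests will be bilateral and based on non-parametric statistics if necessary". It also plans to calculate power and both ICCs from the trial data. The sample-size section names no reference distribution and no degrees of freedom.

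**The concern.** With about 2,500 stays per ward and period, nearly all the uncertainty in an arm comparison comes from variation between wards in their before-to-during change. That variance has to be estimated from 10 wards (two arms), or 15 if all three arms are pooled. With so few units, the critical value and the power should come from a t distribution. Normal quantiles treat the variance as known and overstate power.

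The number of wards is fixed, so this figure is the article's only statement of what the trial can detect. If 44% is paired with 80% power when the real power is nearer 70–74%, the type II error at that effect is about 26–31%, not 20%. A null result printed beside the stated figure would then be over-read. Recalculating power at analysis by the same formula would carry the overstatement into the results.

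**Working it through.** **Inputs.** From Minimal effect demonstrable: p0 = 0.10 in both arms before and in the control arm during; p1 = 0.10 × (1 − 0.44) = 0.056; within-period ICC 0.026; between-period ICC 0.022; m = 2,500 stays per ward and period (or 13,333/5 = 2,667); k = 5 wards per arm; alpha 0.05; power 0.80. From Data analysis: two-sided tests and a logit model.

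**Step 1: reproduce the 44%.** The variance of one ward's change in log odds is

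A/(p0q0) + A/(p1q1) − 2 × 0.022/√(p0q0·p1q1), with A = [1 + (m − 1) × 0.026]/m.

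- A = (1 + 2,499 × 0.026)/2,500 = 0.02639; p0q0 = 0.0900; p1q1 = 0.056 × 0.944 = 0.05286.
- Intervention ward: 0.2932 + 0.4992 − 0.6379 = 0.1545.
- Control ward: 2 × 0.2932 − 0.4889 = 0.0975.
- SE of the contrast: √[(0.1545 + 0.0975)/5] = 0.2245.
- Effect: ln(0.1/0.9) − ln(0.056/0.944) = 0.6275.
- Ratio: 0.6275/0.2245 = 2.795.
- Normal power: Φ(2.795 − 1.960) = 0.798.

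Solving for 80% power gives a detectable reduction of 44.1% at m = 2,500 and 44.0% at m = 2,667. The published figure is recovered.

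**Step 2: replace the normal by a t reference.** Power is the probability that a noncentral t with noncentrality 2.795 exceeds the two-sided 5% critical value. Three df conventions are reasonable: 2 × 5 − 2 = 8 (two arms only), 15 − 3 = 12 (three arms pooled) and 15 − 1 = 14 (wards less one random effect).

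| Reference (m = 2,500) | Critical value | Power at 44% | Reduction detectable at 80% power |
|---|---|---|---|
| Normal | 1.960 | 79.8% | 44.1% |
| t, 14 df | 2.145 | 73.9% | 47.3% |
| t, 12 df | 2.179 | 72.8% | 47.8% |
| t, 8 df | 2.306 | 68.8% | 50.1% |

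At m = 2,667 the t rows become 74.1%, 73.0% and 69.0% for power, and 47.1%, 47.7% and 50.0% for the detectable reduction.

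**Step 3: other routes to 44%.**

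- Two-year intervention volume on the logit scale (2,667 before, 5,333 during): 43.5% with normal quantiles; 46.6–49.4% with t on 14 to 8 df.
- Log scale with 2,500 before and 5,000 during: 44.0% with normal quantiles; 47.3%, 47.9% and 50.3% with t on 14, 12 and 8 df.
- Linear scale, m = 2,500: 49.2% with normal quantiles; higher with t.
- Both intervention arms pooled against control on the logit scale, m = 2,500: 37.5% with normal quantiles; 40–42% with t.

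No t-based variant with 5 wards per arm returns 44%.

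**Step 4: would a normal reference in the analysis make 80% true?** Under the null, 40,000 simulated 5-versus-5 comparisons at the stated ICCs (between-period correlation about 0.022/0.026 = 0.85) rejected as follows:

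- normal critical value, uncorrected sandwich variance: 13.0%
- normal critical value, small-sample-corrected variance: 9.7%
- t on 8 df, corrected variance: 5.8%

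At a true 44% reduction the t test on 8 df rejected 72.6%, a little above the formula's 69% but well short of 80%. The normal test with corrected variance reached 81.9%, but only at the inflated alpha.

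**The case against.** The strongest reply is that nothing is miscalculated. The 44% follows from the listed inputs, the method is a cited one not available here, and the article states neither normal nor t quantiles. That stands in part. A reader might infer that the article declares a normal reference or contains a slip of arithmetic, and it does neither. The normal reference is inferred from the fact that it returns 44% and t does not.

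Second, the size of the shortfall depends on the df convention, which the article does not fix. This also stands, and is why a range is given. All three conventions leave power 6 to 11 points below 80%.

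Third, 13,333/2,500 = 5.33 wards, and with 6 wards per arm t-based values straddle 44% (44.7% at 10 df, 43.1% at 15 df). But 15 wards allocated 1:1:1 are 5 per arm. Even 5.33 wards gives only about 72–77% power (8 to 14 df).

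Fourth, the correction is no larger than the effect of a small ICC change: with normal quantiles, a between-period ICC of 0.021 gives 48.0% and 0.023 gives 39.5%. That is fair as to importance. But input uncertainty runs both ways, whereas this error runs one way: at 12 df the same two ICCs give 52.0% and 42.9%.

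Finally, a reader might infer that the 5% should also be split over the two comparisons with control, lowering power further. The article does not support that: it states a 5% alpha for two distinct interventions, no section requires a split, and a testing order may sit in an analysis plan not shown.

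**Conclusion.** The concern holds in a limited form. The stated combination of a 44% reduction, 80% power and two-sided 5% alpha is one the design with 15 wards does not have. Power at 44% is about 69% (8 df) to 74% (14 df), and 73% at 12 df. The reduction detectable with 80% power is about 50% to 47%, and 48% at 12 df.

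This rests on the article's own rates and ICCs, 5 equally sized wards per arm, a logit-scale contrast of one intervention arm with control, and the inference that normal quantiles were used. Unequal ward volumes would lower power further.

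It should not be read as showing that the design is unsound or that the planned analysis is wrong. The detectable effect moves by 3 to 6 percentage points and the design is unchanged. The article does not itself claim that a null result would exclude 44%, and it plans 95% confidence intervals. Whether those carry a small-sample correction may be settled in the analysis plan. This is a stated figure worth correcting, not a threat to the trial.

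**What to change.** Restate the figure in Minimal effect demonstrable with the reference distribution and df named, for example: *with 15 wards (t reference, 12 df) the minimal detectable reduction at 80% power is about 48%; power at a 44% reduction is about 73%*. If another df convention is adopted, name it and give its figures from the table. Use the same reference distribution and df when power is recalculated as foreseen under Data analysis.

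The cost is a slightly less favourable stated figure. No wards or stays are added, and the randomisation, outcome and model are untouched.

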### Intervention

As usual in the different hospitals of our institution, the MMC is structured using the guidelines of our federation to prepare and standardise the case analysis. A session should be structured to present the case, identify care problems, investigate the causes, analyse the recovery process, and finally propose an action plan. For all three study arms, at least 3 MMCs each year will be carried out in each unit during the 2 years of the intervention. Participants will not be blinded during the trial due to the nature of the intervention (passive feedback and active feedback).

For the control arm, MMCs will be organised during the intervention according to the usual format.

For passive feedback, the local coordinator in charge of MMC will choose the case analysed. A wide dissemination of information will be provided to all health professionals in the unit (medical and paramedical teams) in order to optimise the communication and increase the ownership of the professionals, in order for them to play an active role in error prevention. Therefore, the agenda of the MMC will be widely disseminated by e-mail and/or on paper, then the areas for improvement decided during the meeting, and the regular (monthly) monitoring of progress made. This monthly monitoring will check the implementation of the previous objectives with possible corrections to be made.

For active feedback, it will be first suggested to broaden the choice of adverse events analysed in MMC, which is currently focused on serious events or deaths, by disseminating the list of patients with potential adverse events detected by the triggers. Then, the research group will develop an in situ simulation training programme with scenarios adapted from the cases analysed in MMC. The content of this training programme is based on the experience acquired in the simulation centre of our institution’s medical school. The in situ simulation training will be conducted in the ward during working hours in order to make the experience as close as possible to reality. This training programme is designed according to the main topics identified for the successful implementation of healthcare simulation in patient safety programmes: technical skills, nontechnical skills, assessment, effectiveness, and system probing [29]. Depending on the case to be treated, the scenario may be clinical using a patient simulator, or an interpersonal communication to learn communication skills through the simulation method. Simulation-based interpersonal communication skills training will be implemented when the adverse event is due to a communication problem: from the healthcare team to the patient, from the healthcare team to the family, or from a communication problem within the healthcare team. Depending on the case studied in MMC, the most appropriate type of simulation for each session will be discussed by the simulation team, the health services researchers of our institution, the local MMC coordinator, and the health manager of the ward concerned. After discussion between this pedagogical team, the principal investigator ([name]) will write the scenario according to the pedagogical objectives. Each simulation session will have specific objectives to promote the acquisition of appropriate technical and nontechnical skills (stress management, situational awareness, teamwork, and briefing strategies) [30]. Participants will receive a standardised briefing for each scenario. Then, an inter-professional simulation will be carried out under the responsibility of a trainer of our local centre for teaching by simulation in healthcare. The principal investigator ([name]) will be responsible for the standardised debriefing formats in order to improve situational awareness [31–33]. The debriefing will necessarily be concise with a maximum of 5 key messages for each session. The simulation sessions will be filmed and broadcast live for the entire staff present in the ward. The objective is to involve at least a quarter of the department’s staff (participants or observers). At the end of each session, participants and observers will be asked to evaluate and propose solutions to the problems identified. Figure 3 shows a schedule of study enrolment, interventions and assessments. The recommendations for interventional trials (SPIRIT) checklist is available as Additional file 1.

**Fig. 3 Fig3:**
[figure not shown]
Schedule of enrolment, interventions, and assessments ((as per Standard Protocol Items: Recommendations for Interventional Trials (SPIRIT) figure)

### Data collection and management

The data analysed will come from different sources: all the institution’s information systems, including emergency, operating room, and biology software, as well as patient records detected by the trigger tool methodology.

Our institution’s data management and analysis department (HCL) will extract these triggers from the hospital data warehouse.

The steering committee, composed by the authors, will verified the quality of the MMC, including the number and quality of participants at each meeting. It will be responsible for checking recruitment, ensuring that sites are conducting follow-ups, and checking the completeness and quality of the data. The quality of the MMC will be evaluated annually during a consensus meeting of two researchers who independently will score the quality of MMC, using a yes/no scoring system for each above-mentioned characteristic. The steering committee will meet just before database lock. This meeting will provide an opportunity to decide on issues such as possible requests for unresolved corrections, establish a baseline, and check the quality of the data. The final data set will be available upon request to the authors.

